#### 1360 **7.4 Reporting Procedures**

1361 Note that adverse events are recorded in 1) participant weekly surveys; 2) acupuncturist's CRF's; 3) at  
1362 post-treatment visit by research team. The research team will perform QA check on all of the following  
1363 data (with particularly focus on safety) on a monthly basis: participant daily/weekly surveys, participant  
1364 questionnaires, consent forms, all research team CRF's, acupuncturist's CRF's. Specifically, we will check  
1365 for 1) protocol deviations; 2) all adverse events. We will log these for each participant on Excel  
1366 Spreadsheets (on our lab's HIPPA compliant server), monthly and report all to NCCIH, DSMB and IRB at  
1367 the appropriate time intervals.

1368 Acupuncturists will assess adverse events twice a week at the treatment sessions and will complete the  
1369 Adverse Event CRF. Acupuncturists will also notify the RC in case of adverse events and the RC will  
1370 follow-up with the participant by phone within 3 business days if the adverse events are acupuncture  
1371 treatment related. If adverse events are severe and related to the acupuncture project, DSMB will be  
1372 notified immediately, the treatment will be stopped and the PI will have a consultation with the  
1373 participant within 3 days of the onset of side effects.

1374 Adverse Events will be reported to NCCIH, DSMB, and Stanford IRB annually. Serious Adverse Events that  
1375 are determined to be related to the study will be reported to the IRB by filing a report on the Stanford  
1376 IRB website. A copy of this report will be sent to the NCCIH officer. Unexpected fatal or life-threatening  
1377 Adverse Events related to the intervention will be reported to the NCCIH Program Officer within 7 days.  
1378 Other serious, unexpected, and related Adverse Events will be reported to the NCCIH Program Official  
1379 within 15 days and to the Stanford IRB within 10 business days. Anticipated or unrelated Serious  
1380 Adverse Events will be handled in a less urgent manner but will be reported to the Independent  
1381 Monitor(s), Stanford IRB, and NCCIH in accordance with their requirements. In the annual Adverse Event  
1382 summary, the Independent Monitor(s) Report will state that they have reviewed all Adverse Event  
1383 reports.

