#### 6.2.3 Blinding

Blinding of the participant will be ensured by strict controls in the communications between the acupuncturist and the participant. The acupuncturists will receive one day of hands-on training as well as written materials, and they will attend a refresher workshop 1-2 weeks before seeing their first participants. Strict guidelines on communication with the participant will be provided and will be reinforced during regular provider meetings with the PI ([name]).

Blinding of the assessor. The PI and the research assistant will be the assessors. Only the acupuncturists (treatment providers) will be unblinded. The randomizer will deliver the randomization assignment to the acupuncture provider via secure email.

1183 Individuals authorized to break the blind. The members from the DSMB will meet and assess side  
 1184 effects from both treatment arms and decide if there is a need to unblind and to possibly terminate or  
 1185 modify the problematic treatment.

1186 Circumstances for breaking the blind: We do not anticipate that we will need to break the blind unless  
 1187 we see clear harm (>50% worse from baseline for one group, or >30% participants experience prolonged  
 1188 side effects, e.g. severe pain, persistent hematoma, nausea etc) lasting over two weeks.

1189 Procedures for breaking the blind. We stress that we do not anticipate breaking the blind except for  
 1190 extenuating circumstances where significant harm is caused by the VA or PA treatment. Such  
 1191 circumstances will always be reported to the DSMB and a decision regarding how to proceed will come  
 1192 from the DSMB. Such examples include a) large bleeding and bruising (over three sessions) due possibly  
 1193 to an undiagnosed clotting disorder; b) severe pain due to the treatment as recorded on the participants  
 1194 weekly adverse event report form lasting more than two weeks; c) unresolved nausea, dizziness  
 1195 persistent for more than two weeks.

1196 In terms of procedures for breaking the blind, we will use the following steps.

1197 **Level 1:** The research assistant will be responsible for monitoring the participant's adverse event data  
 1198 gathered via the Android device; additionally, the acupuncturist will monitor and report on side effects  
 1199 from treatment. If any of the above mentioned severe reactions to acupuncture occur (extremely rare),  
 1200 the RC and/or the acupuncturist will report to the PI.

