1201 **Level 2:** The PI will report the event(s) to the DSMB.

1202 **Level 3:** The DSMB will decide, based on the severity and time course of the reported adverse, whether  
 1203 or not to terminate the participation of the participant and at the same time to break the blind. The  
 1204 information of treatment delivered and settings where the adverse event occurred would be important  
 1205 to minimize such events from happening again in the future.

1206 **6.2.4 Treatment Visits**

1207 Treatment Visits. Each participant will receive 12 treatment sessions. For each session, the participant  
 1208 fills out adverse event form at the beginning of the session (except for the first session), the  
 1209 acupuncturist fills out the treatment CRF near the end of the session. Sessions 1, 2, 5 and 12 will contain  
 1210 specific assessments, as outlined below.

1211 Treatment Session 1: 60 minutes

- 1212 • Acupuncturist will perform initial history and physical. History will include similar information as  
 1213 original baseline visit (pain location, duration, character, intensity, medication list, past medical  
 1214 and surgical history, previous allopathic and CAM treatment for back pain; as well as at TCM  
 1215 related question. Physical exam will include pulses, tongue exam according to TCM, as well as  
 1216 lumbar and low extremity palpation, range of motion, as well as anything else can be  
 1217 comfortably performed by the acupuncturist. These details will be recorded in the **Acupuncture**  
 1218 **Intake CRF**.
- 1219 • Most importantly, the acupuncturist will record a) if the participant experiences pain in  
 1220 hips/upper thighs; b) rating of back pain over the last 7 days using an 11-point (0-10) numerical  
 1221 rating scale (NRS).

- 1222 • Treatment will be administered per protocol (see Section 5.1)
- 1223 • Participant will complete **Stanford Expectancy of Treatment** BEFORE and AFTER the 1st
- 1224 treatment
- 1225 • Acupuncturist will complete session record on Visit Notes CRF
- 1226 • Acupuncturist will schedule/confirm next treatment session(s)
- 1227 Treatment sessions 2: 45 minutes
- 1228 • Participant will complete adverse event form before session starts.
- 1229 • Treatment will be administered per protocol (see Section 5.1)
- 1230 • Participant will complete **Vincent Credibility Scale** after the 2nd session.
- 1231 • Acupuncturist will complete session record on Visit Notes CRF

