1288 lack of benefits (analgesia), pregnancy, development of significant medical/psychiatric  
1289 comorbidity or additional pain foci.
- 1290 • Necessary evaluations: Most importantly, we will collect the daily monitoring data and use the  
1291 average pain score from the last 7 days prior to termination to calculate the final primary  
1292 outcome (pain reduction). Depending on the severity of side effects, we will bring the  
1293 participant in for a visit with one of our MD staff, provide appropriate treatments, and monitor  
1294 the participant until the side effects resolve. For details of the type of side effects and  
1295 prospective treatments, please refer to Section 7.3 under "adverse effects."

1296

1297 **7. SAFETY ASSESSMENTS**

1298 Overall, acupuncture is a generally safe procedure with essentially negligible risk for serious  
1299 complications in practiced hands (which is true in our case as all our acupuncturist have >3 years of  
1300 practice experience).

1301 **Potential adverse events:** acupuncture is an extremely safe intervention. For each of the **four**  
1302 **categories of complications**, we have specific ways to handling them as below.

- 1303 • **First**, the most common side effects are minor pain and bruising at the needle insertion sites  
1304 and they typically go away within 2-3 days.
- 1305 • **Second**, some individuals may experience mild vasovagal reaction near the beginning of the  
1306 treatment. If it happens, we will immediately lay the participant supine and monitor. Only if  
1307 these symptoms do not resolve after the participant is laid supine for 5 minutes, we plan to  
1308 vigorously stimulate Du-26 and select Ting points at the toes which are indicated to treat  
1309 vasovagal reactions. If within 2 minutes the symptoms do not subside, we will take the needles  
1310 out, and offer hydration. Most cases resolve with these maneuvers.
- 1311 • **Third**, nausea and dizziness may also occasionally occur but are short-lived. If they do occur, we  
1312 will immediately lay the participant supine and monitor. Only if these symptoms do not resolve  
1313 after the participant is laid supine for 5 minutes, we will insert needles to bilateral MH-6, ST-41  
1314 (indicated to treat nausea), and GV-20 (indicated for dizziness) in the subsequent sessions. If  
1315 the symptoms do not improve after 3 sessions and the participant feels significantly bothered,  

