1316 we will terminate the participant's enrollment.
- 1317 • **Fourth**, complications such as infection, nerve injury and pneumothorax are extremely rare (less  
1318 than one in 10,000). If they do occur, treatment will be terminated, DSMB will be alerted, and  
1319 the participants will be followed and treated by an MD until the symptoms resolve following

1320 standard of care (e.g. antibiotics for infection, x-rays and possibly needle decompression for  
1321 pneumothorax).

- 1322 • **Finally**, adverse reactions will be recorded two ways: by the acupuncturist at the end of each  
1323 session and by the participant on their Android device.

1324 **7.1 Specification of Safety Parameters**

1325 The most common risks in acupuncture are local swelling, bruising, and pain, and less commonly  
1326 transient nausea and dizziness. In the rare case of persistent light-headedness, blood pressure and  
1327 heart rate will be assessed in the office. Most of the monitoring will be done by verbal report by the  
1328 participant and visual exam and palpation of the needled sites by the acupuncturist.

1329 **7.2 Methods and Timing for Assessing, Recording, and Analyzing Safety Parameters**

1330 The surveillance and detection of adverse effects by acupuncture will be accomplished in three layers.

1331 **Layer 1** – the participant: The acupuncturist will explain the common side effects of acupuncture to the  
1332 participant based on a standardized script. Then, the participant will log the presence of any side effects  
1333 on the Android device on a weekly basis. Further, presence of immediate side effects to treatment will  
1334 be reported to and noted by the acupuncturist on the session record.

1335 **Layer 2** – The acupuncturist: he/she will observe and inquire about immediate side effects after each  
1336 treatment, will also note delayed side effects on the session records.

1337 **Layer 3** – The research team (PI and RC) will survey the Android device logs by the participants every 2-4  
1338 weeks and review the presence, time course, and severity of side effects, and intervene if necessary.

1339 **7.3 Adverse Events and Serious Adverse Events**

1340 An **adverse event (AE)** is generally defined as any unfavorable and unintended diagnosis, symptom, sign,  
1341 syndrome or disease which either occurs during the project, having been absent at baseline, or if  

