#### 1388 **7.6 Safety Monitoring**

##### 1389 **Data Monitoring and Safety Board (DSMB)**

1390 The CAM Center DSMB has the following members:

1391 [name], PhD (Biostatistics expertise)

1392 [name], PhD (TCM trials expertise)

1393 [name], MD/PhD (Clinical expertise)

1394 The DSMB will convene every 3 to 6 months after initial recruitment. Safety will be reviewed and  
1395 participant cases will be reported to the members of the DSMB and relevant safety decisions will be

1396 made. The sessions will be open to PI and the mentors. DSMB reports will be sent to NCCIH and Stanford  
1397 IRB within 10 business days of the meeting.

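### The protocol contradicts itself on what follows a severe treatment-related reaction: when treatment stops, when the DSMB hears of it, and who decides whether the participant continues

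*Protocol*

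**What the plan says.** Five places in the protocol deal with stopping one participant because of harm.

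- **Section 7.4 (Reporting Procedures).** The condition is "If adverse events are severe and related to the acupuncture project, DSMB will be" and the action is "notified immediately, the treatment will be stopped", with a consultation between the PI and the participant within 3 days. Severity and relatedness are the only conditions.
- **Section 6.2.3 (Blinding).** The examples of reactions include severe pain caused by treatment, as recorded on the "weekly adverse event report form lasting more than two weeks; c) unresolved nausea, dizziness", the last two again for more than two weeks. Level 1 treats the listed reactions as severe and sends them to the PI. At Level 2 the PI reports to the DSMB. At Level 3, "The DSMB will decide, based on the severity and time course of the reported adverse, whether" or not participation ends, and the blind is broken at the same time.
- **Section 7 (Safety Assessments), third category, nausea and dizziness.** Extra points are needled in later sessions. If "the symptoms do not improve after 3 sessions and the participant feels significantly bothered", then "we will terminate the participant's enrollment". No DSMB step is written.
- **Section 7, fourth category.** For infection, nerve injury or pneumothorax, treatment is terminated and the DSMB alerted.
- **Section 8 (Intervention Discontinuation).** The Investigator withdraws a participant when the intervention is judged to cause side effects that cannot be resolved, or persistent worsening of pain. No time limit is given.

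Sections 5.4.5 and 9.3 define completion: no more than 3 missed sessions, of which (5.4.5) only two may be consecutive.

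**The concern.** For one event, such as severe pain caused by treatment, the sections give different answers to three questions. When is the DSMB told: at once, or after more than two weeks? Does treatment stop automatically, or does someone decide? If someone decides, is it the DSMB or the Investigator?

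The first stake is participant safety: staff at seven treatment sites cannot derive one instruction from the text. The second is the analysis. The number of sessions received determines membership of the per-protocol set. The kind of stop may also determine the source of the outcome. Section 6.2.6 computes the final primary outcome from the last 7 days of daily pain scores when a participant terminates early. Section 5.4.5 collects post-treatment data on non-completers exactly as on completers. Whether a participant has only stopped treatment or has left the study therefore matters, and the safety sections do not keep the two apart.

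**Working it through.** **Inputs.** Two sessions a week for 6 weeks (section 5.1.1); more than two weeks (6.2.3); 3 sessions (section 7); no waiting time (7.4); the completion limits in 5.4.5 and 9.3.

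**Step 1. Reproduce the plan's figure.** 2 sessions/week × 6 weeks = 12 sessions, as stated.

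**Step 2. Put the timings on one scale.**
- 7.4: 0 further sessions.
- Section 7, nausea and dizziness only: 3 sessions ÷ 2 per week = 1.5 weeks.
- 6.2.3: 2 weeks × 2 per week = about 4 sessions before the duration is reached; 4 ÷ 12 = one third of the course.

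So severe related pain meets two timings (0 and about 4 sessions). Severe related nausea or dizziness meets three (0, 3 and about 4).

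**Step 3. Allow for when the reaction begins.** If it begins at session k, only 12 − k sessions remain, so the further sessions before the 6.2.3 duration is reached are the smaller of 4 and 12 − k. This gives 4 for k up to 8, then 3, 2, 1 and 0 for k = 9 to 12.

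**Step 4. Effect on completer status.** Assume every session up to k is attended. Stopping at once leaves 12 − k missed. Stopping after the two-week duration leaves 8 − k missed, or 0 if k is 8 or more.

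| Onset session k | Missed, stop at once | Missed, stop after about 4 more | Status, counting missed sessions only | Status, with the consecutive limit |
|---|---|---|---|---|
| 4 | 8 | 4 | non-completer either way | non-completer either way |
| 5 | 7 | 3 | changes | non-completer either way |
| 6 | 6 | 2 | changes | changes |
| 7 | 5 | 1 | changes | changes |
| 8 | 4 | 0 | changes | changes |
| 9 | 3 | 0 (only 3 remain) | completer either way | changes |
| 10 | 2 | 0 | completer either way | completer either way |

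Status changes for onset at sessions 6, 7 and 8 under either reading of the limit. It also changes at session 5 if only the count applies, or at session 9 if the consecutive limit applies. For onset at session 4 or earlier, or 10 or later, it does not change.

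**Step 5. Compare the decision-makers.** 7.4 names nobody, because the stop is automatic. Section 7 says the team. 6.2.3 says the DSMB. Section 8 says the Investigator. The team and the Investigator may be the same people; the DSMB is not.

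**The case against.** The strongest answer is that these are different acts. Section 7.4 stops treatment, section 7 ends enrolment, section 8 withdraws from the project, and 6.2.3 stands under the procedures for breaking the blind. The protocol itself says that participants who miss more than 3 sessions are not withdrawn. On this reading 7.4 stops needling at once, and 6.2.3 comes into play later if the harm persists. The two-week items are also offered as examples, and the gravest events (infection, nerve injury, pneumothorax) are handled consistently with 7.4.

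Much of this stands. No passage tells anyone to keep treating during the two weeks, so the session count arises only if 6.2.3 is followed instead of 7.4. The 3-session rule concerns symptoms that section 7 calls short-lived and never labels severe.

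The sequential reading still leaves three conflicts. The DSMB is told at once in one section and after more than two weeks in another. The DSMB and the Investigator each hold the decision on ending participation. For nausea and dizziness, 3 sessions and more than two weeks are different triggers for ending participation.

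Stronger readings that the documents do not support:
- *At least four more sessions.* Four requires onset by session 8, and requires 6.2.3 to be followed in place of 7.4.
- *The DSMB would decide too late.* From "The DSMB will convene every 3 to 6 months after initial recruitment" and a 6-week course, a reader might infer this. No passage makes an individual decision wait for a scheduled meeting, and 7.4 provides for immediate notice.
- *Discontinuation will differ between providers or arms.* None of these rules makes the acupuncturist the decision-maker. Table 1 shows penetrating needles and live current only in the verum arm, which makes unequal triggering conceivable, but the protocol gives no rates.

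**Conclusion.** The contradiction is real. It is clearest between 7.4 and 6.2.3 on DSMB notification and on stopping, and between 6.2.3 and 8 on who decides. The third timing, in section 7, applies to nausea and dizziness only, so all three timings meet only in a severe related case of those symptoms.

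The size is conditional: 0 against up to about 4 further sessions, if 6.2.3 displaces 7.4 and onset is by session 8. The consequence for completer status is confined to onset around the middle of the course (sessions 6 to 8, plus 5 or 9 depending on how the limit is read) and assumes full attendance until then. It bears on the per-protocol analysis. Section 5.4.5 makes intention-to-treat the rule for all analyses, which limits the statistical damage but does not settle which outcome source applies after a stop.

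This should be corrected, mainly because it concerns the handling of harm. Which trigger is right is not a statistical question.

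**What to change.** Reconcile sections 6.2.3, 7, 7.4 and 8, and refer to the agreed rule from each of them:

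1. For each event type, one consistent trigger and one named decision-maker who can act within the treatment course.
2. State whether the DSMB is notified of an individual case or decides it. If it decides, say how that happens between scheduled meetings.
3. Define stopping treatment, ending participation and breaking the blind as separate steps, each with its own condition.
4. State which of these steps counts as early termination under section 6.2.6, so that it is clear when the daily-score outcome replaces the post-treatment visit.

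The clinical team and the DSMB should choose the triggers. The cost is a protocol wording change and alignment of DSMB procedures. It needs no additional participants or data.

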#### 1384 **7.5 Follow-up for Adverse Events**

1385 After Adverse Events are discussed by the RA/PI and participant and a decision is made regarding  
1386 continuation of participation, the RC will conduct a 1-month follow-up phone call to the participant. This  
1387 phone call will also be recorded in the Adverse Event CRF.

#### 1388 **7.6 Safety Monitoring**

##### 1389 **Data Monitoring and Safety Board (DSMB)**

1390 The CAM Center DSMB has the following members:

1391 [name], PhD (Biostatistics expertise)

1392 [name], PhD (TCM trials expertise)

1393 [name], MD/PhD (Clinical expertise)

1394 The DSMB will convene every 3 to 6 months after initial recruitment. Safety will be reviewed and  
1395 participant cases will be reported to the members of the DSMB and relevant safety decisions will be

1396 made. The sessions will be open to PI and the mentors. DSMB reports will be sent to NCCIH and Stanford  
1397 IRB within 10 business days of the meeting.

## 1398 **8. INTERVENTION DISCONTINUATION**

1399 Participants will be free to withdraw from the project if they no longer wish to participate. If participants  
1400 do not attend more than 3 sessions of PA or VA project arms, their participation will be considered  
1401 incomplete. However, they will not be withdrawn from the project and will be given the opportunity to  
1402 resume treatments. Since this project is not monitoring any lab values and does not involve drugs, there  
1403 are no such values that would warrant intervention discontinuation. As mentioned above, participant  
1404 mood rating and side effects will be monitored via the Android devices, and participants will be  
1405 withdrawn from the project by the Investigator if it is determined that the intervention is causing the  
1406 negative mood ratings, persistent worsening pain, and/or side effects that cannot be resolved.

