#### **5.4.4 Measures to Promote Adherence**

Measures to promote adherence to treatment protocols by acupuncturists are discussed in Section 5.4.1 above.

Ensuring participant understanding of project expectations

- Knowledgeable and receptive staff: PI and lab managers will train research staff on appropriate languages for consenting as well as setting appropriate expectations for study participants.
- Provide a Welcome Packet with project information and easily found contact information for project staff.

- 1046
- Develop a personal relationship with the participant
- 1047
- Continued outreach: After enrollment, PI will write letter to participant thanking him/her for
- 1048
- their work/participation and outline/remind participant of study timeline. Birthday and
- 1049
- holiday cards may also be sent to the participant periodically.

1050 **5.4.5 Specific Triggers and Stopping Rules**

1051 All analyses performed in this project will be intent-to-treat.

1052 If participants miss more than 3 treatment sessions, their participation will be considered

1053 incomplete. Out of the 3 missed sessions allowed, only two may be consecutive. All non-completers

1054 will have the opportunity to resume treatment even if their data is considered incomplete.

1055 Post-treatment data will be collected on non-completers identically as on the completers. In

1056 addition to ITT, we will also run a per-protocol analysis where the non-completers will not be

1057 included.

1058

1059 **6. STUDY PROCEDURES**

1060

1061 **6.1 Schedule of Evaluations (see next page)**

1062

| Who Completes | Assessment                               | Screening Visit | Baseline Tracking                                                                                  | Pre-Tx Visit | Tx #1 | Tx #2 | Tx 3,4,6-11 | Tx #5 | Tx #12 | Post-Tx Visit | Follow up 3,6,12 mo |
|---------------|------------------------------------------|-----------------|----------------------------------------------------------------------------------------------------|--------------|-------|-------|-------------|-------|--------|---------------|---------------------|
| Participant   | Informed Consent                         | X               |                                                                                                    |              |       |       |             |       |        |               |                     |

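### Section 8 ends project participation partly on worsening pain, and the early-termination rule then replaces the post-treatment PROMIS T-score with a non-equivalent diary score

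*Protocol*

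**What the plan says.** Section 8 (Intervention Discontinuation) treats two groups differently in one paragraph.

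- Participants who miss more than 3 sessions are incomplete, but: "However, they will not be withdrawn from the project and will be given the opportunity to" resume treatment.
- Participants monitored for mood and side effects are to be "withdrawn from the project by the Investigator if it is determined that the intervention is causing the" following: "negative mood ratings, persistent worsening pain, and/or side effects that cannot be resolved".

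Two other places also end participation. In Section 7, nausea or dizziness leads to termination of enrollment if "the symptoms do not improve after 3 sessions and the participant feels significantly bothered". In Section 6.2.3, Level 3, the DSMB decides whether "or not to terminate the participation of the participant and at the same time to break the blind". For infection, nerve injury and pneumothorax, by contrast, Section 7 ends only the treatment.

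Section 5.4.5 states: "All analyses performed in this project will be intent-to-treat". Of those who miss more than 3 sessions, it adds: "Post-treatment data will be collected on non-completers identically as on the completers". Section 9.3 counts every randomized participant with baseline assessments in the ITT set.

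Section 6.2.6 (Handling of Early Termination) uses daily monitoring data, namely the "average pain score from the last 7 days prior to termination to calculate the final primary" outcome. Section 9.5.1 defines that outcome as the change in T-score from the full PROMIS Pain Intensity Instrument between the pre- and post-treatment visits.

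**The concern.** The protocol keeps poor attenders under observation but ends participation for some of those who do badly. Persistent worsening of pain is the unfavourable end of the primary outcome. Whether the post-treatment visit takes place therefore depends partly on the value it would have recorded.

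The diary rule fills the gap in the primary outcome, but with a different quantity. At stake are the comparability of the primary outcome across participants, the responder analysis, the functional and long-term outcomes, and the claim that the analysis is intent-to-treat. Only the verum arm receives penetrating needles and current (Table 1), so the loss could differ by arm. The documents do not show that it would.

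**Working it through.** **Step 1. Do Sections 5.4.5 and 8 collide?** The course is 12 sessions and a non-completer misses more than 3. A participant withdrawn after session 8 or earlier misses at least 12 − 8 = 4 sessions and so also meets the non-completer definition. Section 5.4.5 then calls for post-treatment data, while Section 8 has ended participation in the project. For a withdrawal after session 9 or later with no other missed sessions, Section 5.4.5 does not apply and only Section 8 speaks.

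**Step 2. Is the substitute equivalent?**

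| Feature | Planned outcome (Sections 9.5.1, 3, 6.2.5) | Early-termination substitute (Sections 6.2.6, 5.4.2) |
|---|---|---|
| Instrument | Three PROMIS items on a 5-point scale, converted to a T-score (version 4.2 revision note) | Daily average-pain question from a two-question diary |
| Timing | 1 to 2 weeks after the last session | The 7 days before termination, possibly mid-course |
| Responder status | Defined on the PROMIS T-score or the PROMIS mean-pain item | Not classifiable |
| Completeness | Site visit | Under 50% completion is only a protocol deviation (Section 6.2.2) |

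Section 6.2.6 lists no post-treatment PROMIS among the necessary evaluations. It gives no substitute for RMDQ, for the 3-, 6- and 12-month outcomes (Section 9.5.2), or for the 6-month repeat of the Aim 1 analysis (Section 9.6).

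**Step 3. How large could the effect be at worst?** Inputs from Section 9.2: correlation 0.4, 50 per arm, alpha 0.05, Fisher's transformation. Assumptions: two-sided test, bivariate normality, and the number withdrawn, which the documents do not give.

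The plan's own figure comes first: power = Φ(atanh(r)·√(n−3) − 1.96). With r = 0.4 and n = 50, this is Φ(0.4236 × 6.856 − 1.96) = Φ(0.944) = 0.828, against a stated figure of approximately 80%. It reproduces, slightly on the conservative side.

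Now delete the worst fraction f of outcomes entirely. With c the f-quantile of the standard normal, λ = φ(c)/(1−f) is the upward shift of the mean in SD, v = 1 + cλ − λ² is the remaining variance, and the observable correlation is r′ = 0.4√v / √(0.16v + 0.84).

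| Deleted of 50 | c | λ (SD) | v | r′ | Power, worst deleted | Power, same number lost at random |
|---|---|---|---|---|---|---|
| 2 (4%) | −1.751 | 0.090 | 0.835 | 0.370 | 74% | 81% |
| 3 (6%) | −1.555 | 0.127 | 0.787 | 0.361 | 71% | 80% |
| 5 (10%) | −1.282 | 0.195 | 0.712 | 0.346 | 65% | 78% |

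A simulation gives the same values to within rounding. These rows assume that the withdrawn participants are exactly those with the worst outcomes and that nothing replaces their data. Section 6.2.6 does supply a replacement, so the rows are ceilings and not estimates.

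**The case against.** A reader might infer that Section 8 deletes the worst primary outcomes and so inflates the apparent pain reduction. The documents do not support that. Section 6.2.6 assigns a primary outcome to early terminations, and Section 9.3 keeps these participants in the ITT set. A 7-day average ending at termination for worsening pain records the worsened state, so the lower tail may be kept or even overstated. The direction of any bias is therefore not established.

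Other points on that side also stand:

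- Withdrawal needs a judgement that the intervention is the cause, and two of the three triggers (mood, side effects) are not pain. Selection on the outcome is partial.
- The nausea rule and the DSMB decision concern tolerability and harm, not the pain outcome.
- Section 5.4.5 was written for missed sessions, so its conflict with Section 8 is indirect, through the overlap in Step 1.
- Section 8 sits under a heading about the intervention, so its wording may be loose. No passage says that the automatic surveys, timed from the last day of intervention (Section 6.2.5), are switched off.
- The power figures concern the correlation, which Section 9.6 labels a secondary analysis. Prediction error, the primary analysis, was not simulated.
- A conversion or missing-data method could be set out in an analysis plan not shown here.

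What survives is that the protocol itself fixes two different definitions of the final primary outcome, and does not say whether the planned visit still takes place after withdrawal. An analysis plan can handle missing T-scores, but it cannot collect them afterwards.

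**Conclusion.** The point holds in limited form. Section 8 ends project participation, partly on the primary outcome, for participants whom an intent-to-treat analysis needs to observe. For them the planned T-score is lost or replaced by a score that differs in instrument and timing and cannot enter the responder rule. RMDQ and the later outcomes have no replacement.

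The actual size is unknown, because the documents give no expected number of withdrawals. The ceilings, at an assumed 2 to 5 of 50 in an arm, are power of about 74% to 65% against 83%, and mean reduction overstated by 0.09 to 0.20 SD. They rest on full deletion and perfect selection on outcome, neither of which the protocol prescribes. The change is worth making because it is cheap. No view is taken on when treatment should stop.

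**What to change.** Leave the criteria for stopping treatment, and the authority of the Investigator and the DSMB, as they are. Reconcile Sections 5.4.5, 6.2.3, 6.2.6, 7, 8 and 9.5.1 on data collection:

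- State that participants whose intervention is stopped are still asked, if they consent, to complete the existing post-treatment visit (PROMIS, NRS, RMDQ) and the 3-, 6- and 12-month surveys, as Section 5.4.5 already provides for non-completers.
- In Section 6.2.6, use the 7-day diary average only when the post-treatment PROMIS is not obtained. Analyse it as a sensitivity analysis and do not enter it directly as a T-score.

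The cost is protocol wording plus a few visits after treatment has stopped, which some participants will decline. The visit and surveys already exist.
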